**Methods/design:**

Randomized, controlled, prospective, single-center clinical trial with duration of 12 months will be performed to compare the effect of Dader Method of pharmaceutical care with the usual care process of patients in a psychiatric clinic. Patients diagnosed with BD-I aged between 18 and 65 years who have been discharged or referred from outpatients service of the San Juan de Dios Clinic (Antioquia, Colombia) will be included. Patients will be randomized into the intervention group who will receive pharmaceutical care provided by pharmacists working in collaboration with psychiatrists, or into the control group who will receive usual care and verbal-written counseling regarding BD. Study outcomes will be assessed at baseline and at 3, 6, 9, and 12 months after randomization. The primary outcome will be to measure the number of hospitalizations, emergency service consultations, and unscheduled outpatient visits. Effectiveness, safety, adherence, and quality of life will be assessed as secondary outcomes. Statistical analyses will be performed using two-tailed McNemar tests, Pearson chi-square tests, and Student’s t-tests; a *P* value <0.05 will be considered as statistically significant.

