### Study population

The researchers will recruit 200 volunteer patients diagnosed with BD-I, based on the Diagnostic and Statistical Manual of Mental Disorders, 4th edition (DSM-IV). BD-I patients are more likely to have poor adherence, rapid cycling, suicide attempts, and current anxiety or alcohol use disorder. Psychiatrists will refer patients who might meet the inclusion criteria to the pharmaceutical care program; subsequently, the pharmacist will evaluate whether each patient meets all the inclusion criteria and none of the exclusion criteria, and then invite the patient to participate in the study.

The inclusion criteria will be the following:

• Male or female, between 18 and 65 years of age, and diagnosed with BD-I based on the Diagnostic and Statistical Manual of Mental Disorders, 4th edition (DSM-IV), who have been discharged from or referred by the outpatient service of the SJDC.

• Living in Medellín, Sabaneta, Envigado, Itagüí, Bello, Copacabana, Girardota, Barbosa, Guarne, Rionegro, Marinilla, La Ceja, El Carmen de Viboral, El Retiro, San Vicente, La Unión, and El Santuario (Antioquia, Colombia).

The exclusion criteria will be the following:

• Patients with their first manic episode, schizoaffective disorder, BD-II, cyclothymia, and other bipolar spectrum disorders, personality disorders that seem like BD, and sociopathic disorder.

• Patients with epilepsy, infected with the HIV, chronic decompensated disease (blood pressure values above 180/110 mmHg, total cholesterol above 300 mg/dL, low density cholesterol greater than 160 mm/dL, hemoglobin A1c greater than 9%, oxygen saturation lower than 90%).

• Patients unable to comply with the protocol requirements, including severe alcohol and drug use.

• Pregnancy or breastfeeding.

• Patients with intellectual disability, presence of any cognitive impairment impeding the comprehension and signature of the informed consent form, or illiteracy.

• Patients who refuse to sign the informed consent form (consent must be obtained before any study-related procedures are conducted).

• Patients in electroconvulsive therapy.

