### Study outcomes

#### *Evaluation/assessment variables/measuring instruments*

The primary outcomes to be measured are: (1) the number of hospitalizations; (2) the number of emergency service consultations; and (3) the number of unscheduled outpatient visits. In addition to the information provided by patients and family members about the primary objective, the pharmacist gets the information from the records of medical history of the patients, provided by SJDC.

The secondary outcomes to be measured are: (1) adherence to treatment through serum lithium levels, serum valproate levels, carbamazepine-serum levels, and by the questionnaire of Morinsky-Green (MG) [21]; (2) life quality through the Quality of Life Scale: The Short Form (36) Health Survey Questionnaire [22]; (3) Clinical Global Impression for Bipolar Modified scale, CGI-BP-M [23]; (4) Young Mania Rating Scale for the evaluation of mania [24]; (5) Hamilton Rating Scale for Depression [25]; (6) drug safety through creatinine, liver transaminases, alkaline phosphatase, complete blood count, fasting glucose, thyroid stimulating hormone levels (TSH), total T4 or total thyroxin levels (T4), weight and cholesterol; (7) problems related to necessity, effectiveness, and security of the pharmacotherapy (NOMs to be identified and measured); (8) drug-related problems in drug therapy effectiveness, and safety; (9) the impact of side effects of antipsychotic drugs on health-related quality of life with a specific self-rated instrument: the ‘Tolerability and quality of Life’ (TOOL) questionnaire [26]; and (10) the patient’s satisfaction with the pharmaceutical care service measured through the patient satisfaction questionnaire on pharmaceutical care [27]. Control and intervention groups will be compared in terms of the proportion of changes from baseline to follow-up at 12 months. The information collected at 3, 6, and 9 months is part of the follow-up period of patients, and these data help to complement the secondary outcomes of the trial. Secondary outcomes will handled in terms of the proportion of changes from baseline to 12 months following.

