### Data collection

Data will be collected from November 2011 to June 2013. The study will have a total length of 30 months, but time monitoring of each patient will last 12 months. The recruitment period will be 18 months, and patients will be evaluated during 12 months, starting from the date of their recruitment. Once the enrolment period ends, the final 12 months will be only used to evaluate the latest patients. However, for ethical considerations, all patients will be followed periodically by phone calls and further medical history review in the routine control appointment with the physician. Monitoring and evaluation of the variables related to the study (including questionnaires) will take place as follows: at baseline, which corresponds to the day of study entry, and every 3 months at the patients’ check-ups to complete the year of follow-up. The data obtained in this study will be registered in an electronic database that will include the Morinsky-Green questionnaire to measure medication adherence, the scale SF-36 Health Status Questionnaire to estimate quality of life, the Clinical Global Impression for Bipolar Modified (CGI-BP-M) scale to measure the assessing global of illness, the Young Mania Rating Scale for evaluating mania, and the Hamilton Depression Rating Scale to measure depression. Data regarding medication history, interviews with the pharmacist, health current status, plans of action will be registered as well. Related to the primary outcome, in addition to the information provided by patients and family members, the pharmacist gets the information from the records of medical history of the patients, provided by SJDC.

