### Biostatistical considerations

Data will be analyzed according to the intention-to-treat principle. All patients will be analyzing according to their allocated treatment group. Statistical analysis will be blinded and performed using SPSS version 13.0 (IBM SPSS, Armonk, NY, USA). Control and intervention groups will be compared in terms of the proportion of changes from baseline to 12 months following. Repeated-measures analysis will carry out. Clinical assessments will be made at baseline and every 3 months during the study period. Follow-up will be continuing to complete the year, even if a relapse or psychiatric hospitalization occurred. The main end points of interest are the number and duration relapse events per person-year of follow-up and number of admissions to the hospital due to BD. Data will be reported as means and standard deviations (SD) or as percentages. The Pearson chi-square test (between study groups) and the McNemar test (within-group changes from baseline to follow-up at 12 months) will be used to compare proportions. Comparisons for categorical variables will be conducted by using Chi-square tests (the Fisher exact test when appropriate) and for continuous variables by using the independent-sample t test (Mann-Whitney U test when appropriate). The Mann-Whitney test will be used to compare outcomes between groups. For quality-of-life questionnaire the Student’s t test will be used if sample distribution proves to be normal. Otherwise, the Wilcoxon rank-sum test will be used. The paired Student’s t-test (within-group changes from baseline to follow-up at 12 months) or the independent sample Student’s t-test (between study groups) will be used to compare means; odds ratios (ORs) and 95% confidence intervals (CIs) will be estimated as well. Mean number and duration of relapse events normalized to person-time, will be compared between groups using the Student’s t test. Multivariable analyses will be performed to explain the association of multiple variables associated with the factors significantly related to primary outcome: hospitalizations, readmission, relapse and total number of episodes of illness, number and total days of hospitalizations, days of illness, and days of free intervals per year. The sociodemographic and clinical variables to assess will be: duration previous episodes, severity of depression or mania, polarity of the last episode (manic, hypomanic, depressive, or mixed), co-morbid psychiatric illness, social support, psychosocial factors, educational level, living in rural area, having a history of violence to others, having no insight, non-compliance to medication, lack of practical support from the family. Analysis of depression and mania episodes, adherence to pharmacotherapy and quality of life will be performed, using repeated measure analysis. Comparisons will be analyzed using two-tailed tests, *P* <0.05 will be considered as statistically significant.

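### Change from baseline to 12 months is an ill-defined comparison for the three primary event counts and conflicts with the measures used elsewhere in the article

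*Protocol article*

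**What the plan says.** Under Study outcomes, the protocol article states: "The primary outcomes to be measured are: (1) the number of hospitalizations; (2) the number of emergency service consultations; and (3) the number of unscheduled" (the third count is of outpatient visits). No time window is attached to any of the three.

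The same section gives the comparison rule: "Control and intervention groups will be compared in terms of the proportion of changes from baseline to follow-up at 12 months". It then describes the 3-, 6- and 9-month information as "part of the follow-up period of patients, and these data help to complement the secondary outcomes of the trial", and a further sentence applies the change rule to secondary outcomes by name. The first statement of the rule is therefore not limited to secondary outcomes. Biostatistical considerations repeats it without restriction ("Control and intervention groups will be compared in terms of the proportion of changes from baseline to 12 months following") and adds "the McNemar test (within-group changes from baseline to follow-up at 12 months").

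Data collection fixes the time of the first assessment: "at baseline, which corresponds to the day of study entry". No look-back period for events is given. Study population admits patients "who have been discharged from or referred by the outpatient service of the SJDC", so two recruitment routes are mixed.

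**The concern.** A rating scale has a value on the day of a visit. A number of admissions or consultations has a value only over an interval. Subtracting a one-day baseline from a 12-month entry therefore has no clear meaning until someone decides what is counted before entry, whether the index admission is included, and what interval the 12-month entry covers. The article states the change rule but settles none of these.

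The primary comparison is at stake. Two analysts could follow the text faithfully and reach different primary results. Participants and pharmacist are unblinded, and the Discussion says that the same pharmacist observes both groups and collects the data, so the counting rule should be fixed before the results are seen.

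**Working it through.** **1. The rules side by side**

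| Place in the protocol article | What it implies for the primary outcomes |
|---|---|
| Study outcomes; Biostatistical considerations | Change from baseline to 12 months, all outcomes |
| Biostatistical considerations | McNemar within each group, baseline against 12 months |
| Sample size calculation | Between-group proportion readmitted, no baseline term |
| Biostatistical considerations; Missing data | Relapse number and duration per person-year; admissions for bipolar disorder named as a main end point; hospitalization counts and days in a list that ends with a per-year measure |
| Anywhere | No explicit full-follow-up rule for emergency consultations or unscheduled visits |

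These are different quantities, and the article does not say which is primary.

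**2. The plan's own figure**

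Inputs from Sample size calculation: 50% against 30% readmitted, 95% confidence, 80% power, at least 166 patients. A one-sided 0.05 test with continuity correction gives 83 per arm, or 166. Two-sided formulas give 182 to 206. The sidedness is a separate matter. What counts here is that the calculation compares two follow-up proportions, not two changes from baseline.

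**3. Precision of a change score**

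Assume the change is read as follow-up count minus baseline count, with equal variances and correlation ρ. Randomization gives the change and the follow-up count the same expected between-group difference, so variances can be compared directly. Relative to the follow-up count alone, the change has variance 2(1 − ρ). Linear adjustment for baseline has 1 − ρ².

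| ρ | Change score | Baseline as covariate |
|---|---|---|
| 0 | 2.0 | 1.00 |
| 0.25 | 1.5 | 0.94 |
| 0.5 | 1.0 | 0.75 |
| 0.75 | 0.5 | 0.44 |

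The change score loses precision below ρ = 0.5. Covariate adjustment is at least as good in every row. The article gives no ρ.

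**4. The within-group tests and the index admission**

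Let d be the share of patients recruited at discharge (not given, so taken from 0 to 1). Suppose the index admission is scored as a baseline hospitalization and outpatient referrals score none. With 50% and 30% readmitted in follow-up, the within-group changes in percentage points are 50 − 100d (control) and 30 − 100d (intervention).

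| d | Control | Intervention | Control minus intervention |
|---|---|---|---|
| 0 | +50 | +30 | 20 |
| 0.5 | 0 | −20 | 20 |
| 1 | −50 | −70 | 20 |

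The sign of the McNemar comparison depends on the recruitment mix and on an unstated scoring rule. If nothing counts on the day of entry (the d = 0 row), both arms appear to worsen. If every patient has an index admission, both appear to improve. The expected between-group difference stays at 20 points, because randomization balances the route on average.

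**5. Illustration of one reading of the 12-month entry**

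Assumptions: 50% and 30% are 12-month risks (the article gives no period), the hazard is constant, and the last entry covers months 9-12 only. The three-month risk is 1 − (1 − p)^(1/4):

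- control: 1 − 0.5^0.25 = 15.9%
- intervention: 1 − 0.7^0.25 = 8.5%

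Power is Φ[(Δ − 1.96·√(2p̄(1 − p̄)/n)) / √((p₁(1 − p₁) + p₂(1 − p₂))/n)], two-sided 0.05.

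| Per arm | All 12 months, Δ = 20.0 points | Months 9-12 only, Δ = 7.4 points |
|---|---|---|
| 100 | 82.8% | 35.6% |
| 83 | 75.3% | 30.4% |

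A constant rate places 9/12 = 75% of expected events before month 9. This is power for a between-group proportion, not for a change score.

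**The case against.** A reader might infer that the trial will discard events in months 0-9. The documents do not support that as a conclusion. The abstract says that "Study outcomes will be assessed at baseline and at 3, 6, 9, and 12 months after randomization", and the control-group and intervention descriptions have the primary variables assessed at the quarterly appointments. Study outcomes and Data collection also draw them from clinic records, and Data management stores hospitalizations and appointments. Biostatistical considerations continues follow-up through the year after a relapse and lists hospitalization measures alongside a per-year term. The sentence on interim data says that they complement the secondary outcomes, not that they are barred from the primary counts. No section says that the 12-month entry covers only the last quarter. All of this stands, so the fall in power illustrates a reading and is not a forecast.

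A reader might also infer that counting the index admission biases the treatment comparison. It does not in expectation: the recruitment route is fixed before randomization. It mainly adds noise and distorts the within-group tests.

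Finally, a look-back window is a detail that an article may leave to a fuller document. That is fair for the window alone. But the change-from-baseline rule is stated, twice, in a form that covers the primary outcomes, and it is that rule which fits badly. The chi-square, t and Mann-Whitney comparisons also named do not rescue it, because the text does not say whether they apply to follow-up counts or to changes.

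**Conclusion.** The point holds as a badly fixed primary comparison. As stated, change from baseline is ill-defined for the three counts, can be less precise than a direct comparison of follow-up counts (up to twice the variance at ρ = 0, assuming equal variances), and makes the McNemar results depend on how an index admission is scored. It also conflicts with the proportion that sizes the trial and with the per-year measures. Emergency consultations and unscheduled visits are the most exposed, since no explicit full-follow-up rule covers them.

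Loss of the first nine months is possible under the text but not demonstrated. The drop from about 83% to 36% with 100 per arm depends on all three assumptions in step 5 of the working.

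**What to change.** In Study outcomes and Biostatistical considerations:

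- Limit the change-from-baseline comparison, and the sentence on 3-, 6- and 9-month data, to scales and laboratory values.
- Define each primary outcome as all events from randomization to month 12, taken from the visits and the clinic records, with the index admission excluded.
- Compare these counts between groups with follow-up time as exposure.
- Drop the McNemar tests for these three outcomes.
- If a prior-period count is wanted, take it from the records over a stated window and use it only as an optional baseline covariate.

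The cost is wording and minor analysis work, plus one field from records already consulted if the optional covariate is used. No visits or patients are added.

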### Withdrawal or termination from study

According to the investigator’s judgment or when applicable, patients and their families should be informed of circumstances under which their participation may be terminated by the investigator without the subject’s consent. Patients and their families should also be informed of procedures for safe and orderly termination should they decide to withdraw from the study before it is completed. In addition, patients may leave the study at any time. Patient’s data concerning the reason for withdrawal before completing the treatment will be registered and archived for statistical evaluation. Specific reasons for withdrawal or termination from study are: (1) voluntary withdrawal from the patient; (2) intervention is harmful to the health of the patient; (3) patient’s death; (4) development of exclusion criteria during the study or other safety reasons; or (5) non-compliance of the protocol. The intention-to-treat principle will be kept at all times and all subjects will be analyzed according to their allocated treatment group.

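### The only between-group safety comparison specified is change from baseline to month 12, so abnormalities corrected earlier do not show in it and withdrawals for harm enter it as imputed values

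*Protocol article*

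**What the plan says.** The list of secondary outcomes (Study outcomes, Evaluation/assessment variables/measuring instruments) includes, as item 6, "drug safety through creatinine, liver transaminases, alkaline phosphatase, complete blood count, fasting glucose", followed by thyroid tests, weight and cholesterol. The same section sets the comparison for all secondary outcomes: "Secondary outcomes will handled in terms of the proportion of changes from baseline to 12 months following". Biostatistical considerations repeats it for the two groups: "Control and intervention groups will be compared in terms of the proportion of changes from baseline to 12 months following".

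Safety is measured more often than that. The control-group and intervention-group sections both provide for meetings at 3, 6, 9 and 12 months. The control-group section says safety is among the variables assessed at each appointment. Data collection schedules the study variables at baseline and then "every 3 months at the patients’ check-ups to complete the year of follow-up". Of the values at months 3, 6 and 9, the outcomes section says only that "these data help to complement the secondary outcomes of the trial".

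Biostatistical considerations announces a repeated-measures analysis in general terms and later names its outcomes: "Analysis of depression and mania episodes, adherence to pharmacotherapy and quality of life will be performed, using repeated measure analysis". Drug safety is not among them.

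Reasons for withdrawal include "2) intervention is harmful to the health of the patient", the development of exclusion criteria, and other safety reasons. Missing data states that missing values will be multiply imputed under a missing-at-random assumption, with all randomised patients kept in the analysis.

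**The concern.** The trial's aim, stated in Background, includes increasing the safety of treatment. The intervention pursues this by detecting drug problems during the year, reporting them to the psychiatrist and following them until they are resolved. An abnormal value at month 3 or 6 may therefore be normal again by month 12, and this may happen sooner in the intervention arm, which has weekly contact. A comparison at month 12 cannot separate an arm with few abnormalities from an arm with many that were quickly corrected. Both are of interest, but they are different findings. The rule set for drug safety gives one figure for the two.

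**Working it through.** **The texts side by side**

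- Measurement: every 3 months.
- Comparison: baseline to month 12, stated in the outcomes section and again in Biostatistical considerations.
- Interim data: described as complementary, with no method.
- Repeated measures: the outcomes named are mood episodes, adherence and quality of life.

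The rule is stated, so this is more than detail left to an analysis plan.

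**What month 12 can miss**

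The article gives no rate of safety abnormalities, so the inputs below are assumptions.

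- q = probability that an unaffected patient is newly abnormal at the next 3-monthly visit, taken as 5%.
- r = probability that an abnormality is corrected by the next visit, varied from 0 to 1.
- Visits: four (months 3, 6, 9 and 12).

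Ever affected = 1 − (1 − q)^4 = 1 − 0.95^4 = 18.5%.

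Prevalence at each visit: p(v) = p(v−1) × (1 − r) + [1 − p(v−1)] × q, with p(0) = 0.

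For r = 0.5:
- visit 1: 5.0%
- visit 2: 0.05 × 0.5 + 0.95 × 0.05 = 7.25%
- visit 3: 0.0725 × 0.5 + 0.9275 × 0.05 = 8.3%
- visit 4: 0.0826 × 0.5 + 0.9174 × 0.05 = 8.7%

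Share missed = (ever affected − month-12 prevalence) / ever affected.

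| r | Ever affected | Abnormal at month 12 | Share missed |
|---|---|---|---|
| 0 | 18.5% | 18.5% | 0% |
| 0.3 | 18.5% | 11.7% | 37% |
| 0.5 | 18.5% | 8.7% | 53% |
| 0.8 | 18.5% | 5.9% | 68% |
| 1 | 18.5% | 5.0% | 73% |

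The last row takes month-12 prevalence as the 5% newly abnormal at that visit. The recursion does not let a patient be corrected and newly abnormal in the same interval, and it gives 0.9524 × 0.05 = 4.8%, or 74% missed.

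With q = 10%, 34.4% are ever affected. Month-12 prevalence is 21.8%, 16.2% and 11.1% at r = 0.3, 0.5 and 0.8, so the shares missed are again 37%, 53% and 68%. The share depends mainly on the speed of correction.

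**Occurrence mixed with correction**

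- Arm A (q = 10%, r = 0.8): 11.1% abnormal at month 12, 34.4% ever affected.
- Arm B (q = 5%, r = 0.3): 11.7% abnormal at month 12, 18.5% ever affected.

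Month 12 looks equal, although nearly twice as many patients in arm A were affected (34.4 / 18.5 = 1.86).

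The reverse can also occur. With q = 5% in both arms and r = 0.8 against 0.3, month 12 shows 5.9% against 11.7%, although 18.5% of each arm was ever affected.

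**Withdrawals**

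A patient withdrawn for harm has no observed month-12 value. Imputation under missing at random draws one from patients with a similar recorded history who stayed. If withdrawal followed harm not captured by a recorded value, the assumption is doubtful. If it followed a recorded value, the assumption may hold, but the comparison then contains a predicted month-12 value and not the harm itself. This route can involve item 6 directly: total cholesterol above 300 mg/dL is an exclusion criterion, developing an exclusion criterion is a reason for withdrawal, and cholesterol is an item 6 variable.

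**The case against.** A reader might infer that harm before month 12 is not counted at all, or that the trial cannot show how many patients were harmed. The article does not support that.

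- Negative outcomes associated with medication, drug-related problems and a side-effect questionnaire are separate secondary outcomes (items 7 to 9). They fall under the same month-12 rule, but they are recorded.
- The general repeated-measures sentence excludes no outcome, although the later list omits safety.
- Reasons for withdrawal are registered for statistical evaluation.
- The imputation models use all observed time points, so an abnormal value seen before withdrawal is not discarded.

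Two further inferences go too far. One is that falls in some patients must cancel rises in others: the rule speaks of a proportion of changes, which need not be a mean. The other is that a high serum drug level can never count as a safety problem because levels are listed under adherence: items 7 and 8 could capture it.

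The size is also open. Nothing in the article shows that changes in weight, cholesterol, glucose or thyroid tests reverse within 3 months, and with no correction month 12 misses nobody.

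The strongest objection concerns the remedy. Resolving drug problems is the purpose of the intervention, so a better state at month 12 is a real benefit. In the equal-incidence example, an any-visit count alone would show 18.5% in both arms and hide it. This stands, and it is why the month-12 comparison should be kept.

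Reference-range tables are commonly left to an analysis plan, and none is shown. Their absence is therefore not the finding. The finding is that the rule which is stated covers month 12 alone.

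**Conclusion.** The point holds in this form: the only between-group comparison specified for drug safety is baseline to month 12, and the article defines no between-group use of the interim safety values or of withdrawals for harm. Abnormalities corrected before month 12 do not show in that comparison, and patients withdrawn for harm contribute imputed values.

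At an assumed 5% of new abnormalities per interval, the share of ever-affected patients missed runs from 0% to 73%, according to an unknown speed of correction. These figures illustrate the mechanism and do not predict the trial's result. The article supports the conclusion that the month-12 comparison by itself does not show how often harm occurred. It does not support the conclusion that earlier harm goes unrecorded.

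**What to change.** Keep the baseline-to-month-12 comparison and add the following to Biostatistical considerations:

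1. By arm, compare the proportion of patients with any post-baseline item 6 laboratory value outside the laboratory's reference range, at any visit up to month 12 or withdrawal. Use observed values and show the number of assessments per arm beside the proportion.
2. By arm, list withdrawals for harm or other safety reasons, from the reasons already registered.

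Weight has no laboratory reference range and stays with the month-12 comparison.

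The cost is a little more analysis work, since the values and withdrawal reasons are already due to be collected. The drawback is that patients with fewer visits have fewer chances to be counted, so an arm with more early withdrawals could look safer. The number of assessments and the withdrawal listing make this visible but do not remove it.
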